### Statistical Analyses

3.12

All sites will be allowed a three‐month post‐implementation period of transition before outcome measurement. Temporal confounding will be mitigated through the use of models (e.g., interrupted time series analysis) which adjust for secular trends. Given the stepped‐wedge cluster randomised design, analyses will explicitly include fixed effects for time period and intervention status, and random effects for site (cluster) to account for ICC. With only eight clusters, we will apply the Kenward–Roger correction to adjust standard errors and *p* values are not inflated due to small number of clusters. Data analysis will be conducted using Python (3.11) and R (version 4.4.1).

The percentage of surveillance recommendations that match with Australian guidelines will be calculated from audit data, and the prevalence of individuals lost to follow‐up, prevalence of those with acceptable colonoscopy quality, and incidence rates for advanced neoplasia and adverse events will be summarised using descriptive statistics. All measures will be directly compared to each site's own baseline measures in a paired manner using McNemar's tests for proportions, Wilcoxon and Kruskal–Wallis signed‐rank tests for continuous measures and mixed‐effects Poisson regression for incidence rates. Analyses will be conducted on an intention‐to‐treat basis. A prespecified generalised linear mixed model (GLMM) with a logit link will be used for the primary binary outcome (guideline concordance) including fixed effects for time period and intervention, random intercepts for clusters and adjustment for potential confounders (e.g., age, indication and baseline quality metrics). To address the small number of clusters (*K* = 5), we specify that inference will be based on cluster‐preserving parametric bootstrap for both the intervention coefficient and marginal contrasts. Multiple comparisons across secondary outcomes will be controlled using Holm–Bonferroni correction to limit type I error. Additional sensitivity analyses will include (i) cluster‐level summaries with Kenward–Roger correction, (ii) generalised estimating equations with small‐sample corrected SEs and (iii) permutation tests at the cluster level. If national guideline text changes during the trial, an indicator for the new guideline will be included, and analyses will be repeated using both old and new mapping.

Where relevant, univariate followed by multivariable modelling will be undertaken by adding variables considered clinically important or statistically significant from the univariate model to adjust for confounding effects. Hospitals will be treated as random effects, and main effects will be the intervention group; that is, before and after implementation of the intervention. Missing data will be handled using multiple imputation under the missing‐at‐random assumption. For bowel preparation quality, missing values will be imputed as ‘adequate’ in the primary analysis, reflecting routine clinical documentation where poor preparation is explicitly noted, with sensitivity analyses applying conservative rules assumption imputing missing values as ‘poor’.

Multivariable generalised linear models and pairwise comparisons will be used to assess the association between patient‐reported measures (such as satisfaction with the colonoscopy experience) and acceptance of the digital healthcare approach. Thematic analysis will be conducted to establish clinical end‐user opinions on the surveillance program. Prespecified subgroup analyses will assess intervention effects across patient age, sex, socioeconomic status (by postcode linkage) and hospital location, with multiplicity controlled via Holm–Bonferroni correction. To ensure equitable healthcare delivery, analyses will include age groups ≥ 75 years, comorbidity burden (based on the Charlson Comorbidity Index categories), socioeconomic status and regional vs. metropolitan location.

Quality of life measures will be used to calculate the incremental costs before and after implementation of the intervention per quality‐adjusted life‐year gained (QALY) in a model‐based economic evaluation. Implementation costs will be obtained from administrative data. The economic evaluation will adopt a health‐system perspective with a 12‐month time horizon, 5% annual discounting and QALY derivation from EQ‐5D‐5L value sets. Probabilistic sensitivity analyses will assess parameter uncertainty, and reporting will align with CHEERS 2022 guidelines [43]. Patients will be recruited consecutively at each site, with reminders and follow‐up strategies implemented to maximise retention. Missing responses in surveys and quality‐of‐life instruments will be addressed using multiple imputation under the missing‐at‐random assumption, consistent with the approach for clinical outcomes.

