### Inclusion and Exclusion Criteria

3.2

All colonoscopies conducted at participating hospitals will be included (Table 1), regardless of indications and patient risk factors. Individuals who opt out of having their health data audited will be excluded from the study. The hospital coverage captures approximately 50% of the colonoscopies completed in South Australia, and > 80% of procedures completed in government‐run public hospitals [33].

**TABLE 1 cam471456-tbl-0001:** South Australian public hospitals implementing the integrated nurse and digital surveillance program.

Locality	Hospital network	Included hospitals
Adelaide metropolitan	Southern Adelaide Local Health Network	Flinders Medical Centre Noarlunga Health Services
	Northern Adelaide Local Health Network	Lyell McEwin Hospital Modbury Hospital
	Central Adelaide Local Health Network	The Queen Elizabeth Hospital The Royal Adelaide Hospital
Regional	Riverland Mallee Coorong Local Health Network	Riverland General Hospital
	Eyre and Far North Local Health Network	Port Lincoln Hospital

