### Automated Clinical Data Collection

3.5

Relevant data (Table 2) will be sourced from each hospital's existing clinical databases. Clinical data provided in structured fields, such as in colonoscopy reports and medical records, will be cleaned and collated into relevant fields within a clinical registry in the digital platform (computer software). Relevant elements from synoptic reports and unstructured or free‐text clinical data, such as those used in histopathology and surgical reports, will be extracted and cleaned through the spaCy library in Python for natural language processing (NLP) and rule‐based regular expressions. The NLP system will account for synonyms and variations in terminology, allowing differentiation between key terms such as ‘no high‐grade dysplasia’ versus ‘high‐grade dysplasia’. The cleaned data (Table 2) will then be collated within the digital platform.

**TABLE 2 cam471456-tbl-0002:** Demographic and clinical data variables required for generating automated colonoscopy surveillance intervals.

Category	Data source	Variables collected
Demographics	Electronic medical record	Patient identifiers Age Sex Body measurements Postal address Family physician contact details Family history of colorectal cancer or genetic syndrome Personal risk factors (e.g., genetic syndromes or past colorectal cancer or neoplasia)
Colonoscopy provision	Colonoscopy reporting system	Date of procedure Proceduralist Indication for colonoscopy
Colonoscopy quality	Colonoscopy reporting system	Intubation distance Withdrawal time Bowel preparation score
Lesion detection	Colonoscopy reporting system Histopathology reports Surgery reports	Number of lesions Lesion morphology Lesion size Anatomical location Removal technique and completeness Lesion histology Presence and extent of dysplasia or invasive cancer
Other clinical factors	Electronic medical record, Colonoscopy reporting system	Comorbidities or other relevant colonoscopic observations Medications
Adverse events	Electronic medical record, Colonoscopy reporting system	Post‐polypectomy bleeding Bowel perforation Hospitalisation Death

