### Data Governance and Safety Monitoring

3.9

All study data will be stored on secure institutional servers compliant with role‐based access control, multifactor authentication and encrypted data transmission between participating sites. Automated audit logs will record all data modifications and algorithm interactions. To mitigate automation bias, nurse coordinators will review and confirm all algorithm‐generated recommendations using a structured checklist before acceptance into the patient record. A data and safety monitoring plan will oversee potential harms such as delayed colonoscopies or missed advanced neoplasia.

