### Outcome Parameters

3.10

All study outcomes will be compared between baseline and post‐intervention measures. The primary outcome is the proportion of automated interval recommendations for surveillance colonoscopy that match those derived from a prespecified ruleset directly based on the Australian guidelines. This ruleset serves as the gold standard for interval assignment and is explicitly programmed from the most recent national surveillance criteria. Algorithm outputs will be independently compared against this reference ruleset, with nurse recommendations serving as a secondary comparator. Validation will be conducted blinded to algorithm outputs to avoid bias, and any discrepancies between algorithm, ruleset and clinical recommendations will be adjudicated by an independent gastroenterologist panel.

Secondary outcomes include:
The timing of the scheduled colonoscopy in relation to the recommended timeframe, with ‘on‐time’ colonoscopy defined as occurring within ±6 months of the due date specified by guideline recommendations.The time taken to review the colonoscopy outcomes and communicate the prescribed surveillance interval with the patient and family physician.The prevalence of individuals lost to follow‐up.The prevalence of patients with acceptable bowel preparation quality, complete intubation and adequate withdrawal time.The incidence rate for advanced neoplasia (with hierarchical classification prioritising invasive CRC > stage 0 CRC > advanced adenoma), including CRC, adenomatous polyps or sessile serrated lesions ≥10 mm in size, with villous change, or with high‐grade dysplasia, sessile serrated lesions with any dysplasia and any traditional serrated adenoma.The incidence rate for adverse events (e.g., bleeding, perforation, hospitalisation and death).Acceptability of the intervention to patients and clinical teams.Cost‐effectiveness of the intervention.Among the secondary outcomes, those relating to colonoscopy quality metrics and timeliness are confirmatory and prespecified, whereas patient‐reported measures and thematic feedback analyses are exploratory.

Trial findings will be reported according to the CONSORT‐AI extension guidelines [42].

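### As worded, the three-month transition drops each network's first three months of live use from the between-phase comparison of adverse events and recall failures

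*Protocol article*

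**What the plan says.** Protocol article, section 3.12 (Statistical Analyses): all sites are allowed three months after implementation as a "period of transition before outcome measurement". No outcome is exempted. The same section states the analysis principle: "Analyses will be conducted on an intention"-to-treat basis.

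Section 3.10 (Outcome Parameters) opens with "All study outcomes will be compared between baseline and post"-intervention measures. Its secondary outcomes include the time taken to communicate the interval, the prevalence of loss to follow-up, advanced neoplasia, and "The incidence rate for adverse events (e.g., bleeding, perforation, hospitalisation and death"). Section 3.12 sets these against each site's own baseline, with mixed-effects Poisson regression for incidence rates.

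Three other sections bear on the point:
- Section 3.2: "All colonoscopies conducted at participating hospitals will be included", with no exclusion by calendar time.
- Section 3.5, Table 2: the adverse-event variables sourced from clinical systems include "bleeding Bowel perforation Hospitalisation Death".
- Section 3.9: "A data and safety monitoring plan will oversee potential harms such as delayed colonoscopies or missed advanced neoplasia".

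**The concern.** A transition period is a reasonable choice when the question is how well the program works once it has settled. It fits less well for outcomes that show what happens while a service changes its recall process.

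Under section 3.8, an implemented network uploads reports, the algorithm proposes an interval, a nurse approves it, and the patient and family physician are told. Patients seen in the first three months therefore receive the intervention. Section 3.7 describes an external validation before results are fed back to users, but only at the first site.

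If these months are left out of the comparison, the trial's reported contrast says nothing about recall failures or adverse events during start-up. That matters to anyone planning the scale-up that the Discussion anticipates.

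**Working it through.** **Step 1. Does the rule reach safety and recall outcomes?** Section 3.12 delays outcome measurement at all sites. Section 3.10 defines adverse events, loss to follow-up and communication time as outcomes, and compares all outcomes between phases. No exception is stated, so the literal answer is yes.

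**Step 2. Are the data lost?** No. Section 3.2 includes every colonoscopy. Table 2 lists the adverse-event variables. Section 3.8 records the time to communication and the reasons for discrepant intervals. Section 3.9 logs algorithm interactions and sets up safety oversight. None of these is suspended during the transition. The gap is in the comparison, not in the recording.

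**Step 3. How much intervention time is affected?** The article gives no figure to reproduce.

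Inputs: five networks, one crossing every 6 months, each with at least 12 months of intervention (section 3.8), and a 3-month transition (section 3.12). Assumption: follow-up ends 12 months after the last crossover.

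- Exposure: 36 + 30 + 24 + 18 + 12 = 120 network-months.
- Transition: 5 × 3 = 15 network-months.
- Share overall: 15 / 120 = 12.5%.
- Share in the last network: 3 / 12 = 25%.

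Section 3.11 describes a different layout, with seven 3-month periods. With one network crossing per step, the post-implementation cells number 6 + 5 + 4 + 3 + 2 = 20. The transition removes one cell per network, so 5 / 20 = 25%.

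**Step 4. How many episodes?** Section 3.11 gives an average of 1417 episodes per 3-month period but does not make the unit clear.

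| Reading of 1417 | Episodes in the transition windows |
|---|---|
| Total over all networks | 1,417 |
| Per network | 5 × 1417 = 7,085 |
| Per hospital | 8 × 1417 = 11,336 |

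The ceiling of 10,000 colonoscopies per network per year (section 3.8) gives at most 5 × 10,000 × 3/12 = 12,500.

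**Step 5. Which measures does the 3-month rule actually govern?** Sections 3.1 and 3.8 repeat the audits and the key performance indicators no earlier than 6 months after implementation. For those measures the later start already applies, and changing the transition rule alters nothing. The rule governs what is taken continuously from the registry: adverse events, and recall failures recorded there.

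**Step 6. What is left open?** Section 3.12 does not say whether the exclusion follows the date of the colonoscopy or the date of the event. The choice decides whether a later event in a patient first seen during the transition is counted.

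**The case against.** The strongest reply is that the transition sentence only fixes when comparative measurement starts. Harms in those months are still recorded and overseen, and a nurse confirms every recommendation (sections 3.8 and 3.9). Bleeding and perforation follow the procedure, which the recall process does not change. Harm from a wrong interval would mostly appear when the next colonoscopy is due, usually after the transition. Reporting windows for safety may also be set in the monitoring plan or an analysis plan that is not shown.

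Much of this stands, and it rules out several stronger readings that a reader might draw:

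- *That early harm goes uncounted, or that monitoring cannot see it.* The recording and oversight provisions contradict the first, and nothing ties the monitoring to the analysis window.
- *That the comparison is biased in favour of the intervention.* This would follow if early months carry more failures. That is plausible, but the article gives no figure for it, and nurse confirmation works against it.
- *That the rule breaches intention-to-treat.* A uniform, prespecified transition at all sites is not selective removal of patients after the fact. The two statements are simply not reconciled.
- *That a patient given a wrong interval in month 1 never enters a measured cohort.* No section bars such a patient's later colonoscopy.

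What the reply does not remove is the wording. Recording and overseeing an event does not put it into the reported comparison. Nor is this a detail merely left to another document: section 3.12 states a rule for all outcomes, and an analysis plan that follows it would inherit the gap.

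**Conclusion.** The point holds in limited form. As worded, the between-phase comparison of adverse events, loss to follow-up and interval communication omits each network's first three months of live use. On 6-month steps, with follow-up ending 12 months after the last crossover, that is 12.5% of intervention time overall and 25% in the last network. Under the seven-period layout it is 25% overall. The episode count cannot be narrowed beyond 1,417 to 11,336 until the unit of 1417 is stated.

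These shares measure how much exposure is left out. They do not measure bias, whose direction and size are not established. The change is worth making because it is cheap and affects what the trial can say about harm during rollout.

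**What to change.** Amend section 3.12 to say that:

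1. the three-month transition exclusion applies to effectiveness outcomes only;
2. adverse events and registry-recorded recall failures (loss to follow-up, interval not communicated) are reported from the go-live date at each network;
3. patients whose colonoscopy falls in the transition are kept for these outcomes;
4. results are given at least descriptively, split into months 0–3 and after month 3.

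Audit-derived measures and key performance indicators keep their start at 6 months or later.

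The cost is a few lines of text and slightly more analysis, using data the registry is already set to hold. The safety figures may look less favourable if the early months perform worse.

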### Study Setting and Design

3.1

The SCOPES program will provide automated recommendations for colonoscopy surveillance intervals, which align with the timings recommended in the Australian guidelines [6], for people at elevated risk for developing CRC across five South Australian local hospital networks (inclusive of 8 hospital sites). The process will be overseen by a nurse‐coordinated team, with the digital processes streamlining existing clinical resources, using natural language processing to convert reports to structured data and provide appropriate algorithm‐based surveillance recommendations. These recommendations will be validated against existing surveillance colonoscopy data from the nurse‐led SCOOP program which has been well annotated, audited and cleaned over the years, with reviews conducted by multiple experts. These data were collected manually for a range of elevated risk indications related to personal and familial factors.

Hospital audits and patient‐reported measures will determine compliance with national guidelines for surveillance colonoscopy and consumer satisfaction before program implementation. The program will be implemented in one hospital network at a time, across five different hospital networks, and evaluated using a stepped‐wedge cluster trial design. Audits will be repeated after at least 6 months of implementation. Feasibility assessments will determine the accuracy, acceptability and cost‐effectiveness of the surveillance program compared to current practices.

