### Implementation of the Digital Process

3.8

This trial will compare a control phase (usual practice) with an intervention phase (the nurse‐coordinated program integrated with digital processes [i.e., SCOPES]) using a stepped‐wedge cluster trial design [40]. Implementation will commence in the second year of the study, where one new hospital network will have the intervention implemented every 6 months, until all five included South Australian hospital networks receive the intervention. The stepped‐wedge design can provide greater statistical power than a randomised parallel group cluster trial design under certain conditions, such as moderate intra‐cluster correlation (ICC), adequate cluster size and multiple steps, with fewer time constraints in the introduction of the digital processes [41]. Each hospital network is expected to perform up to 10,000 colonoscopies per year and will receive the intervention phase for at least 12 months.

Figure 1 provides an overview of the digital processes. Following the automatic upload of colonoscopy and associated pathology data into the clinical registry, the SCOPES algorithm will provide a surveillance recommendation. Each recommendation will be reviewed and approved by a trained nurse. In cases where the nurse and algorithm identify discrepant surveillance interval recommendations, conflicts will be resolved by a third‐party nurse or proceduralist as appropriate. All reasons for discrepant surveillance intervals will be recorded for quality improvement purposes.

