### Sample Size and Power

3.11

The stepped‐wedge cluster randomised trial includes five local health networks (cluster) with eight participating hospitals, contributing an average of 1417 colonoscopy episodes per 3‐month period (adjusted for 10% attrition) across seven sequential periods (one baseline and six rollout steps). Assuming an ICC of 0.01, a baseline guideline concordance of 60%, and an expected post‐implementation improvement to 75% (15% absolute increase), the design archives approximately 90% power at a two‐sided *α* = 0.05 under a binomial mixed‐effects model. Power was estimated via simulation (*n* = 1000 iterations per effect size), incorporating cluster and period fixed effects. A power curve (Figure S1) illustrates sensitivity to effect size assumptions, a stepped‐wedge design diagram (Figure S2) depicts the rollout sequence, and a summary of power estimates across effect sizes is presented in Table S3.

For the patient‐reported outcomes, assuming eight hospitals with paired before and after implementation (100 participants per hospital per period, total *N* = 1600), we estimate > 80% power (*α* = 0.05, two‐sided) to detect a small‐to‐moderate standardised mean difference (Cohen's *d* ≈ 0.25–0.30) in EQ‐5D‐5L scores, accounting for within‐cluster correlation (ICC ≤ 0.02) and within‐period correlation of repeated measures (*ρ* ≈ 0.5). This is appropriate for evaluating meaningful changes in patient‐reported measures at the hospital level.

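### Section 3.12 counts eight clusters in one sentence and five in another and puts random effects on sites and hospitals, although the intervention crosses over by network, of which there are five

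*Protocol article*

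**What the plan says.** On the rollout, section 3.1 states "The program will be implemented in one hospital network at a time", and section 3.8 adds that "one new hospital network will have the intervention implemented every 6 months". Table 1 lists two hospitals in each of the three metropolitan networks and one in each of the two regional networks, eight in all.

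On the cluster, section 3.11 describes a trial that "includes five local health networks (cluster) with eight participating hospitals". The networks carry the label and the hospitals sit inside them.

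Section 3.12 uses several units:

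- The general model statement puts random effects on the site and equates site with cluster. The next sentence begins "With only eight clusters, we will apply" and names Kenward–Roger.
- The passage on the primary logit GLMM has random intercepts for clusters and continues "To address the small number of clusters (*K* = 5), we specify that inference will be based on" a cluster-preserving parametric bootstrap.
- Kenward–Roger returns as a sensitivity analysis on cluster-level summaries, beside permutation tests at cluster level. The unit is not restated for either.
- The paragraph on multivariable modelling says "Hospitals will be treated as random effects".

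Nowhere does the article describe hospitals nested within networks.

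**The concern.** In a stepped-wedge trial, the units that cross over independently determine how much the data can say about the intervention. Two hospitals that switch on the same date because their network switches are not two independent crossovers. An analyst who takes eight as the cluster count will use the wrong reference distribution or permutation set. An analyst who takes five will not. The bootstrap depends on this too, because the same section equates cluster with site, so the level at which it preserves clusters is open.

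The small-sample method is also left loose. Kenward–Roger is derived for Gaussian linear mixed models and does not carry over directly to a logit GLMM. Yet the sentence that introduces it follows a model statement about the analyses in general and does not exclude the primary outcome. If this is left as it stands, the cluster count and the correction could be settled after results are seen.

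**Working it through.** **1. The count.** Networks by hospitals from Table 1: 2 + 2 + 2 + 1 + 1 = 8 hospitals in 5 networks. Sections 3.1 and 3.8 give one crossover date per network, so there are five crossover dates and five independent crossover units. The K = 5 sentence agrees with sections 3.1, 3.8 and 3.11; the eight-cluster sentence does not. The article's power figure of about 90% does not bear on this and is not used.

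**2. Permutation set (no correlation assumption).**
- Orders of five networks: 5! = 120, smallest one-directional p = 1/120 = 0.0083.
- Eight hospital labels over the same schedule: 8!/(2!·2!·2!) = 40320/8 = 5040, smallest p = 1/5040 = 0.0002.

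Most of the 5040 arrangements split a network across dates, which the design does not allow.

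**3. Type I error with hospitals as units.**

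Inputs from section 3.11: ICC 0.01, 60% and 75% concordance (midpoint 0.675), seven periods, 1417 episodes per 3-month period. The article does not say whether 1417 is a total, per network or per hospital, so all three were run: 1417/8 = 177, 1417 × 5/8 = 886, or 1417 per hospital-period.

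Assumed, not in the article: cluster autocorrelation (CAC) and the share of between-cluster variation that hospitals in a network have in common.

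Model: normal hospital-period means with no intervention effect. Within-cell variance is 0.675 × 0.325 = 0.219 divided by the cell size; between-cluster variance is about 0.01 × 0.219 = 0.0022. A fraction CAC is constant over time and 1 − CAC varies by period. The analysis has unit and period fixed effects and estimates the residual variance. Residual df are 8×7 − 8 − 6 − 1 = 41 with hospitals as units and 5×7 − 5 − 6 − 1 = 23 with networks. There were 40,000 runs per setting, at nominal 5%.

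| Setting | Unit | 177 | 886 | 1417 |
|---|---|---|---|---|
| CAC 1 (constant over time) | hospital | 5.1% | 5.1% | 5.0% |
| CAC 0.8, none shared | hospital | 5.1% | 5.1% | 5.1% |
| CAC 0.8, half shared | hospital | 6.0% | 8.1% | 8.2% |
| CAC 0.8, all shared | hospital | 7.3% | 11.3% | 11.9% |
| CAC 0.8, all shared | network | 5.0% | 5.1% | 4.9% |

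**4. How far the reference distribution matters.** With K − 2 df, which the article does not specify, the two-sided 5% critical value is 2.447 for eight clusters (6 df) and 3.182 for five (3 df), a ratio of 1.30 at equal standard error. This is a different test from step 3, where the critical value on 41 df is about 2.02. Applied to the same kind of hospital-level statistic at 886 per cell (CAC 0.8), the 6-df value rejects in only 1.9%, 3.6% and 5.7% of runs for none, half and all shared. The figures in steps 3 and 4 must not be combined.

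**5. Would intercepts alone repair it?** No. With CAC 0.8, an analysis with a hospital intercept and only binomial variation within cells rejects 11.9% (177) to 40.7% (1417) when all variation is shared. It still rejects 9.3% to 32.0% when none is. That part comes from omitting a cluster-by-period effect, not from the choice of unit. Nesting hospitals in networks adds no such effect, and a parametric bootstrap from a model without one inherits the gap.

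**The case against.** The best defence is that the primary method can largely be identified. The passage specific to the primary outcome gives K = 5 and the bootstrap, section 3.11 labels the networks as clusters, and Kenward–Roger comes back only as a sensitivity analysis. The eight-cluster sentence can be read as covering other analyses, including continuous outcomes, and the hospital random effects as belonging to a separate multivariable model. Much of this stands. A reader might infer that two analysts are bound to report different primary p-values; the text makes that possible, not certain. What the defence leaves open is the site-equals-cluster wording, the permutation unit, and a count of eight that is wrong for a network rollout whichever analysis it governs.

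The second defence is that inflation is conditional, and this stands in full. A reader might infer that the eight-cluster analysis is anti-conservative outright, or that intervals must be 30% wider with five. The article gives only an ICC. It says nothing on autocorrelation or on whether hospitals in a network share period effects, and without sharing the error rate is about 5%. The 30% holds the standard error fixed and uses degrees of freedom that the article never names.

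Third, section 3.11 deliberately sizes the patient-reported outcomes on eight hospitals. That is fair as a sampling count, so the number eight need not vanish from the article.

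**Conclusion.** The point holds as a contradiction within section 3.12, and the rollout described elsewhere in the article resolves it: five networks are the independent crossover units. That conclusion and the permutation count (120 against 5040) need no assumption about correlation.

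The effect on type I error is conditional. With hospitals as units and residual df it is about 7–12% if all between-cluster variation is shared within networks at CAC 0.8, about 6–8% if half is shared, and about 5% if correlation is constant over time or period variation is purely hospital-level. These figures come from a normal approximation to cell means. They do not simulate the planned logit GLMM, Kenward–Roger or the bootstrap, and they do not show that the primary analysis as intended is invalid. The correction is needed because the article itself fixes the unit inconsistently, and the unit governs the primary inference.

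**What to change.** In section 3.12:

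- Replace eight clusters with five networks, and define the cluster as the network for the stepped-wedge intervention effect. Define site, or stop using it for cluster.
- In the primary logit GLMM, specify random intercepts for network and for hospital nested within network, plus a network-by-period random term.
- Base primary inference on the parametric bootstrap generated from that model at network level.
- Permute networks only.
- Confine Kenward–Roger to the Gaussian analyses (cluster-level summaries and continuous outcomes), with network as the top level.
- Let the eight-hospital figure stand as a sampling count for the patient-reported outcomes, while stating that the network is the crossover unit there too.

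The cost is a text change before analysis, and possibly a wider confidence interval. With 120 orders, the permutation test cannot give a one-directional p below 0.0083.
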